### 2.2. Outcome Variables

Outcome variables will be measured by a blind evaluator, member of the research team. Data will be collected at baseline, during intermediate assessments at weeks 4, 8, and 12 throughout the structured program, and at a follow-up assessment at week 16, depending on each specific variable, described as follows.
*Primary outcomes:* measured at baseline, at weeks 8 and 12—during and after the structured intervention—and at week 16 after the follow-up period.
Participation: measured with the Spanish version of the Young Children’s Participation and Environment Measure (YC-PEM) [30]. The YC-PEM provides insights into family members’ perspectives on the participation of children from 0 to 5 years old in various activities at home, preschool, and the community. For each activity type, the frequency of participation is rated on a scale from 0 to 7 (0 = never; 7 = one or more times a day). Participation level is rated on a 5-point scale (1 = little involvement; 5 = very involved), and desired changes in participation are recorded as yes or no. Additionally, the impact of environmental characteristics and resources on participation is rated on a scale from 1 to 3 (1 = usually difficult/usually not; 3 = generally helps/usually yes).Functional ability: assessed using the Pediatric Evaluation of Disability Inventory–Computer Adaptive Test (PEDI-CAT) questionnaire [31]. Parents or caregivers complete the PEDI-CAT through an adaptive computer platform. The PEDI-CAT includes a bank of items across two domains: Mobility (75 items, ranging from basic motor skills to more complex skills, including the use of walking devices) and Social/Cognitive (60 items covering interaction, communication, daily cognition, and self-control).Quality of life: evaluated using the Spanish version of the Pediatric Quality of Life Inventory (PedsQL)-Neuromuscular module [32]. The PedsQL is a parent-reported tool designed to evaluate perceptions of the child’s quality of life. It includes three dimensions: 17 questions on neuromuscular disease, 3 questions on communication, and 5 questions about family resources. Responses range from 0 (never) to 4 (almost always), which are converted into a score from 0 to 100. Scores are interpreted as follows: 100—never; 75—almost never; 50—sometimes; 25—frequently; and 0—almost always.*Secondary outcomes:*Learning of powered mobility: assessed with the Assessment of Learning Powered Mobility (ALP) [33]. The ALP describes 8 levels of performance (1 = beginner; 8 = expert) in using a powered mobility device, based on five categories: attention level; activity and movement; comprehension of the mobility device; expressions and emotions; and interaction and communication [34]. The ALP levels will be assessed weekly to help guide families on the strategies to use during their sessions and ensure consistent progress.Functional goals: measured with the goal attainment scale (GAS) [35] at baseline and at weeks 4, 8, 12, and 16 assessments. The goals focus on the use of powered mobility in the child’s natural environment and will be developed in collaboration with the child’s family and/or caregivers.Parental stress: assessed with the Spanish version of the Parenting Score Index-Short Form (PSI-SF) [36] at baseline and weeks 8, 12, and 16. The PSI-SF is a 36-item self-reported questionnaire that includes three subscales: parental distress (PD), parent–child dysfunctional interaction (PCDI), and difficult child (DC).Satisfaction with home intervention: scored with the Spanish version of the Client Satisfaction Questionnaire (CSQ-8) [37] at weeks 4, 8, and 12. The CSQ-8 measures overall satisfaction with the received service through 8 items scored on a scale from 1 to 4. The total score ranges from 8 to 32, with higher scores indicating greater satisfaction.Satisfaction with the use of the powered mobility device: assessed with the Spanish version of the Quebec User Evaluation of Satisfaction with assistive Technology Version 2.0 (QUEST 2.0) [38] at week 16 by the end of this study. The QUEST 2.0 is a self-administered instrument designed to assess satisfaction with various assistive technologies and related services. It comprises two subscales for devices and services. Each item is rated from 1 (not satisfied) to 5 (very satisfied). The device subscale contains 8 questions addressing the following dimensions: size, durability, weight, safety, fit, comfort, ease of use, and effectiveness. The services subscale contains 4 questions evaluating the provision of services, professional services, repairs, and follow-up support for the device.

### 2.3. Study Flow

This study will last 16 weeks. Participants in the experimental group will undergo a structured powered mobility intervention, consisting of 30 min sessions conducted three times a week for 12 weeks. Following this, there will be a 4-week follow-up period during which children in the experimental group have unrestricted use of the powered mobility device. In contrast, participants of the control group will continue with their usual routines during the intervention period. After the 12-week intervention phase, the control group (waiting list) will receive the same powered mobility intervention as the experimental group. Figure 1 illustrates the *AMEsobreRuedas* study flowchart.

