## Abstract

**Background**: Young children with spinal muscular atrophy type 1 (SMA1) have limited independent mobility and participation that may lead to cognitive development delays. Implementing early powered mobility in interventions may help them to learn self-initiated movement, play, and having fun to participate in natural settings. The aim of this study is to evaluate the effectiveness of an early power mobility intervention for increasing participation, functional ability, and quality of life in young children with SMA1. **Methods**: AMEsobreRuedas is a randomized waiting list controlled clinical trial. A sample of 24 children (10 months-5 years old, with SMA1) will be randomly allocated to two groups. The experimental group will perform a family-centered intervention with powered mobility for 16 weeks in their natural environment: a 12-week-structured program three times a week; and a 4-week follow-up with free use of the powered mobility device. The control group (waiting list) will keep their routine and will receive the same intervention after the experimental group. Five assessments will be carried out at baseline and weeks 4, 8, 12, and 16. Primary outcomes are participation (YC-PEM); functional ability (PEDI-CAT); and quality of life (PedsQL-Neuromuscular module). **Results**: It is expected that this study will provide further knowledge about the positive impact of powered mobility for the analyzed variables. Moreover, family engagement in the intervention and establishment of functional goals may help to add valuable information about real needs in future research. **Conclusions**: Early powered mobility could increase the opportunities for children with SMA1 to learn to move independently and participate in their natural environment.

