### 2.6. Structured Intervention (Weeks 1 to 12) with the Powered Mobility Device

The powered mobility intervention will be family-centered, lasting for 12 weeks, with three 30 min sessions per week in each child’s natural environment, such as home, community, and school settings.

The structured intervention will be guided by an experienced pediatric physical therapist or occupational therapist, who will collaborate in this study, for the implementation of strategies to enhance mobility with the device. Before starting the intervention, the therapists will undergo an 8 h training session conducted by an expert researcher in powered mobility, a member of the research team. This training will cover general powered mobility concepts, how to assess the child’s level using the ALP instrument, and intervention strategies tailored to each ALP level. Additionally, case studies on powered mobility learning will be discussed.

Training sessions will focus on teaching participants about cause and effect through operating the MROCs, such as pressing the joystick to move and releasing it to stop. Families will be instructed on how to adapt the environment to suit the child’s needs and driving conditions, as well as how to use natural play to encourage the child’s driving for environment exploration.

During the structured intervention period, the weekly sessions will be organized as follows:**First Weekly Session:** each week, the therapist will conduct the session for approximately one hour. The first 30 min will be dedicated to addressing the family’s needs, evaluating the child’s progress using the ALP, and teaching the family the strategies and structure for the remaining 30 min of training. It is essential for a family member to be present in this session to learn the strategies to be used in the subsequent sessions.**Second and Third Weekly Sessions:** these sessions will be conducted by the families and last for 30 min each. They will carry out the training with the MROC, using the strategies they learned during the first session of the week with the therapist.

All sessions will be recorded to allow the therapists and research assessors to review them and then discuss how to optimize the training. Additionally, a member of the research team will conduct weekly follow-up meetings. Families will be required to complete a document detailing the timing of each session, the child’s behavior, family perceptions, and any other relevant observations.

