### 2.7. Follow-up Period (Weeks 13 to 16)—Free Use of Powered Mobility Devices

In the final 4 weeks of this study, the children will have unrestricted use of the powered mobility device, allowing them to use it for as long as they want. During this follow-up period, the photovoice method [44] will be employed, guided by participatory action research (PAR) principles [45] and the patient and public involvement approach (PPI) [46,47]. Families will be trained to take high-quality photographs of their children using the device during everyday activities. They will be provided with detailed instructions on how to take the photos, including some guiding questions (see Figure 6), and the dates they have to send the photographs to the research team. Additionally, a script with five guiding questions will be supplied to assist in capturing relevant and informative images. 

Each family will be instructed to take at least 4 pictures per week, for a total minimum of 16 over the follow-up period. After the families send all the pictures to the research team, there will be an online discussion group meeting between families and the research team to review the photographs and explore the experiences related to the use of the MROC. An adapted version of the SHOWED methodology [44] will be used (see Figure 7).

All stages will be conducted remotely using a free app, as illustrated in Figure 8.

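### The waiting-list start is ambiguous (after week 12 or after week 16); on the more literal reading of Section 2.3, the week-16 group comparison is not treated versus untreated

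*Protocol article*

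**What the plan says.** **Control start.** Section 2.3 states: "After the 12-week intervention phase, the control group (waiting list) will receive the same powered mobility intervention as the experimental group". Until then, "participants of the control group will continue with their usual routines during the intervention period". The Abstract words it differently: "The control group (waiting list) will keep their routine and will receive the same intervention after the experimental group". It also says that the experimental group "will perform a family-centered intervention with powered mobility for 16 weeks in their natural environment", which it splits into 12 structured weeks and 4 weeks of free device use.

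**What counts as the intervention phase.** Section 2.6 is headed "Structured Intervention (Weeks 1 to 12) with the Powered Mobility Device". Section 2.7 treats weeks 13 to 16 separately, as a follow-up period with unrestricted use of the device.

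**Measurements.** Section 2.2 measures the three primary outcomes (YC-PEM, PEDI-CAT, PedsQL neuromuscular module) at baseline, at weeks 8 and 12, and "at week 16 after the follow-up period". The PSI-SF, a secondary outcome, is measured "at baseline and weeks 8, 12, and 16".

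**Analysis.** Section 2.8 assigns outcomes with more than two measurements to a repeated measures ANOVA, which is to locate differences between groups or between time points. It neither names a last randomised comparison nor sets week 16 apart.

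**The concern.** In a waiting-list trial, the randomised comparison lasts only until the controls begin treatment. If they begin once week 12 is complete, the week-16 visit compares children who have finished the structured programme and had four weeks of free use with children who may be a third of the way through the same programme. A between-group ANOVA over all four measurements would treat that visit like the others.

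The bias has a known direction. Any early gain in controls narrows the group difference at week 16, so an effect that lasts in the experimental arm could look as if it were fading. That matters here because Section 3 anticipates continued progress and lasting benefit through the follow-up period. If controls begin only after the week-16 assessment, the problem does not arise. The document does not say clearly which applies.

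**Working it through.** The plan states no figure that bears on this point, so the check sets the texts side by side and counts exposure.

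**Inputs**
- Structured programme: three 30-minute sessions a week for 12 weeks (Sections 2.3 and 2.6).
- Experimental course: 12 + 4 = 16 weeks (Abstract, Section 2.3).
- Primary outcomes and PSI-SF: baseline and weeks 8, 12 and 16 (Section 2.2).
- Analysis: repeated measures ANOVA for more than two measurements (Section 2.8).

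**Step 1: the two readings of the control start**

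| Text | Start after week 12 | Start after week 16 |
|---|---|---|
| Section 2.3, read with the headings of 2.6 and 2.7 | the more literal reading | possible, since 2.3 does not say that the start is immediate |
| Abstract, with a 16-week experimental course | possible, if only the structured part is meant | the more natural reading, but no week is named |

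Each text leans a different way, and neither rules out the other reading.

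**Step 2: control exposure at the week-16 visit**
- Full structured dose: 3 × 12 = 36 sessions; 36 × 0.5 h = 18 h.
- Start after week 12: at most 3 × 4 = 12 sessions, or 6 h. That is 12/36, one third of the dose.
- Start after week 16: 0 sessions.

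The 12 is a ceiling. Section 2.5 requires individual device adjustment and family training beforehand, which may delay the first session.

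**Step 3: measurements affected under a week-12 start**
- Primary outcomes: 3 instruments × 3 post-baseline visits = 9 comparisons, of which the 3 at week 16 are affected.
- PSI-SF: 1 of 3 post-baseline visits.

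**Step 4: how far week 16 can move a summary**

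Section 2.8 names no contrast, so this is an illustration. Week 16 has weight 1/4 in a group main effect over four measurements and 1/3 in mean post-baseline minus baseline. Suppose the true effect is equal at weeks 8, 12 and 16, and controls have gained a share c of it by week 16. The mean post-baseline difference then keeps (1 + 1 + (1 − c))/3 of its size:
- c = 0: 100%
- c = 0.25: 92%
- c = 0.5: 83%
- c = 1: 67%

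The documents give no time course of effect, so c is an assumption and no value is preferred.

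**Step 5: precision lost by stopping the randomised comparison at week 12**

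With equal variances s² and equal correlations r between visits, the variance of the mean of k post-baseline values minus baseline is s²(1 − r)(1 + 1/k).
- k = 3: factor 1 + 1/3 = 1.333.
- k = 2: factor 1 + 1/2 = 1.5.
- Ratio: 1.5/1.333 = 1.125, whatever the value of r. The square root is 1.061, so the confidence interval is about 6% wider.
- The group-by-time degrees of freedom fall from 3 (four measurements) to 2 (three measurements).

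This loss is measured against an uncontaminated week 16.

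**The case against.** A reader might infer that the Abstract and Section 2.3 flatly contradict each other, one fixing week 16 and the other week 12. The documents do not support that. The Abstract names no week, and Section 2.3 does not say that controls start immediately. A start after week 16 can be fitted to both.

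Other text points the same way. Section 2.3 gives the study a duration of 16 weeks, Section 2.7 treats weeks 13 to 16 as its closing weeks, and Section 2.2 places the device-satisfaction questionnaire at week 16 as the study ends. If the study closes at week 16, control treatment may lie entirely after it. This counts for something but does not settle the matter. Sixteen weeks may equally be the length of each child's course, since a full control course ends at week 12 + 16 = 28 or 16 + 16 = 32, beyond week 16 on either reading. Figure 1, the study flowchart, is not available here and may show the start. If it does, the two sentences should match it.

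On the analysis, it is fair to say that Section 2.2 already labels week 16 a follow-up assessment, that Section 2.3 describes the follow-up period for the experimental group, and that an analysis plan could end the group comparison at week 12. Silence on that detail would be no fault. But the control start is a design fact that the protocol itself has to fix. The visits and the ANOVA, followed as written, carry week 16 into the group comparison.

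Finally, the bias is conservative and limited to one visit. That stands, and it limits the seriousness of the point.

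**Conclusion.** The control start is ambiguous between after week 12 and after week 16. On the more literal reading of Section 2.3, the week-16 measurements of the three primary outcomes and the PSI-SF are not treated versus untreated, with up to 12 of 36 structured sessions already given to controls. Section 2.8 does not keep that visit out of the between-group ANOVA.

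The effect would be to shrink the week-16 difference by an unknown amount, toward no effect. This rests on controls starting soon after week 12 and gaining something within four weeks; the documents establish neither. It would go too far to infer that the randomised comparison as a whole is compromised: weeks 8 and 12 remain valid on either reading. The point is worth correcting because one visit in three for each primary outcome depends on it and the correction is cheap.

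**What to change.** State one control start, in the same terms, in Section 2.3 and the Abstract, and make sure that Figure 1 agrees.

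- **If controls start after week 12:** limit the randomised between-group ANOVA to baseline, week 8 and week 12 for the primary outcomes and the PSI-SF, and report week 16 as within-arm follow-up of the experimental group. This changes wording only; no visit or instrument is dropped. The cost is one fewer post-baseline measurement in the randomised comparison, with the roughly 6% wider interval derived above.
- **If controls start after the week-16 assessment:** say so in Section 2.3 and keep week 16 in the comparison. All three post-baseline measurements stay randomised. If the intended start was week 12, the cost is four more weeks of waiting for control families.

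Either choice should be fixed before outcome data are seen.

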### 2.4. Intervention Features

It is very important for families to understand both the implementation of the intervention and the operation of the powered mobility device, specifically a modified ride-on car (MROC). Proper training is essential to ensure that children can effectively use the device in their natural environments [39,40]. Figure 2 provides an overview of the key characteristics of interventions involving powered mobility for young children with mobility limitations.

The Rehabilitation Treatment Specification System (RTSS) framework will be used to detail the components of the intervention (Figure 3) [41,42,43]. 

### 2.5. Adaptation of the Powered Mobility Device

Prior to the beginning of the intervention, a face-to-face meeting will be held to individually adjust the powered mobility device that was chosen to be modified (Figure 4). During this meeting, a comprehensive training session will also conducted for the children and their families in order to address the management of the MROC, so they can take it home to use it during the powered mobility intervention. 

The modifications and adaptation of the device will be performed based on each participant’s individual needs. They may include the placement of larger wheels, adding protective bumpers, adjusting seats, and customizing controls, among other changes (see Figure 5). These modifications may be either permanent or temporary, depending on the progress towards achieving the specific functional goals set for each child.

### 2.6. Structured Intervention (Weeks 1 to 12) with the Powered Mobility Device

The powered mobility intervention will be family-centered, lasting for 12 weeks, with three 30 min sessions per week in each child’s natural environment, such as home, community, and school settings.

The structured intervention will be guided by an experienced pediatric physical therapist or occupational therapist, who will collaborate in this study, for the implementation of strategies to enhance mobility with the device. Before starting the intervention, the therapists will undergo an 8 h training session conducted by an expert researcher in powered mobility, a member of the research team. This training will cover general powered mobility concepts, how to assess the child’s level using the ALP instrument, and intervention strategies tailored to each ALP level. Additionally, case studies on powered mobility learning will be discussed.

Training sessions will focus on teaching participants about cause and effect through operating the MROCs, such as pressing the joystick to move and releasing it to stop. Families will be instructed on how to adapt the environment to suit the child’s needs and driving conditions, as well as how to use natural play to encourage the child’s driving for environment exploration.

During the structured intervention period, the weekly sessions will be organized as follows:**First Weekly Session:** each week, the therapist will conduct the session for approximately one hour. The first 30 min will be dedicated to addressing the family’s needs, evaluating the child’s progress using the ALP, and teaching the family the strategies and structure for the remaining 30 min of training. It is essential for a family member to be present in this session to learn the strategies to be used in the subsequent sessions.**Second and Third Weekly Sessions:** these sessions will be conducted by the families and last for 30 min each. They will carry out the training with the MROC, using the strategies they learned during the first session of the week with the therapist.

All sessions will be recorded to allow the therapists and research assessors to review them and then discuss how to optimize the training. Additionally, a member of the research team will conduct weekly follow-up meetings. Families will be required to complete a document detailing the timing of each session, the child’s behavior, family perceptions, and any other relevant observations.

### 2.7. Follow-up Period (Weeks 13 to 16)—Free Use of Powered Mobility Devices

In the final 4 weeks of this study, the children will have unrestricted use of the powered mobility device, allowing them to use it for as long as they want. During this follow-up period, the photovoice method [44] will be employed, guided by participatory action research (PAR) principles [45] and the patient and public involvement approach (PPI) [46,47]. Families will be trained to take high-quality photographs of their children using the device during everyday activities. They will be provided with detailed instructions on how to take the photos, including some guiding questions (see Figure 6), and the dates they have to send the photographs to the research team. Additionally, a script with five guiding questions will be supplied to assist in capturing relevant and informative images. 

Each family will be instructed to take at least 4 pictures per week, for a total minimum of 16 over the follow-up period. After the families send all the pictures to the research team, there will be an online discussion group meeting between families and the research team to review the photographs and explore the experiences related to the use of the MROC. An adapted version of the SHOWED methodology [44] will be used (see Figure 7).

All stages will be conducted remotely using a free app, as illustrated in Figure 8.

